#### 2. Subject-requested exit.

1) Patients who are unwilling or unable to continue with the clinical trial may request withdrawal from the trial from the principal investigator, leading to trial discontinuation. This includes cases where the patient cannot complete the entire course of treatment, leading to incomplete data collection affecting efficacy and safety assessments; 2) Subjects who, although not explicitly requesting withdrawal from the trial, no longer accept medication or testing and become lost to follow-up.

### Sample size

The sample size calculation was performed using PASS (version 2021) with the “Comparison of two independent sample rates” calculation module. A power of 80% and an alpha level of 0.025 for a one-sided test and a superiority test were used. Based on a previous study by our team [22], the flare rates of acute gouty arthritis after 12 weeks of placebo treatment were 63.2%, and for the group treated with the QTF was 38.5%. Calculations yielded sample sizes of N1 = N2 = 61 for both the intervention and control groups, considering a dropout rate of 20%. In total, 144 patients with intermittent gout will be included, with 72 patients in both the intervention and control groups.

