### Randomization and blinding

A multi-center competitive stratified block randomization method was utilized. Random numbers for the multi-center group were generated using the corresponding randomization procedure in SAS software (version 9.4). These random numbers, alongside their corresponding drug codes, functioned as unique identifiers for participants. After conducting necessary baseline assessments, all eligible patients who met the inclusion criteria and signed informed consent forms will be randomly assigned to either the intervention or control group in a 1:1 ratio. The randomization design and numbers were provided by Jiangsu Famous Medicine Co., Ltd. The relevant parameters and results of the randomization scheme will be recorded by Zhejiang Chinese Medical University (the research design unit). Apart from the outcome evaluators and staff at the drug production center, all researchers and patients remained unaware of treatment allocation. The QTF granules and placebo granules were identical in odor, color, and packaging, ensuring blinding. Distribution details will be disclosed to researchers only when necessary for drug administration. Products were delivered directly to patients according to their allocation codes. In emergencies, the research design unit will promptly provide researchers with randomized numbers and treatment allocations. All participants will strictly adhere to confidentiality regulations to protect patients’ personal privacy information.

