### Statistical analysis

The statistical analysis for this trial will be conducted based on the Per-Protocol (PP) and Intent-to-Treat (ITT) data, conducted by Jiangsu Famous Medicine Co., Ltd., situated in Nanjing, China. Different analysis methods will be employed depending on the type of data measurement or counting.

For the primary outcome, the number of gout flares in each group will be compared using t-tests or Wilcoxon rank-sum tests, with center effects controlled through covariance analysis. For count data, such as time span to the first occurrence of gout flares, duration of acute gouty arthritis recurrence, pain visual analog scale score, HAQ-DI, and safety analysis indicators (like routine blood tests), the same methods will be applied. Measurement data, including the recurrence rate of acute gouty arthritis and the incidence of adverse events, will be analyzed using chi-square tests or Fisher’s exact tests, with center effects controlled through binary or multinomial logistic regression analysis. All hypothesis tests in this study will be two-sided, with a significance level of 0.05. Differences will be considered statistically significant when p < 0.05. SAS version 9.4 will be used for all statistical analyses.

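### 61 per arm with 20% dropout requires 77 per arm (154 in total); the planned 72 per arm (144) covers only about 15% loss and falls short of the stated 80% power

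*Protocol article*

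**What the plan says.** All the figures are in the Sample size section of the protocol article.

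- Error rate and power: "A power of 80% and an alpha level of 0.025 for a one-sided test and a superiority test were used".
- Control rate: "the flare rates of acute gouty arthritis after 12 weeks of placebo treatment were 63.2"%.
- Intervention rate: "for the group treated with the QTF was 38.5"%.
- Result and dropout: "Calculations yielded sample sizes of N1 = N2 = 61 for both the intervention and control groups, considering a dropout rate of 20"%.
- Enrolment: "In total, 144 patients with intermittent gout will be included, with 72 patients in both the intervention and control groups".

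The total of 144 recurs in the Abstract and under Patients' eligibility and criteria. Randomization and blinding confirms the allocation: "randomly assigned to either the intervention or control group in a 1:1 ratio". Statistical analysis sets the test level: "All hypothesis tests in this study will be two-sided, with a significance level of 0.05". No section gives a 15% dropout rate or any other step from 61 to 72.

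**The concern.** The section prints its inputs, its result and its enrolment figure together, and the last step does not follow. If 61 per arm must remain after one patient in five is lost, 72 per arm is too few. If 61 already included dropout, the rise to 72 would have no explanation.

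The trial would be reported as having 80% power after 20% loss, and on its own inputs it does not. The dropout allowance matters in this design. The Exit criteria remove patients for adherence below 80% or above 120%, for medication outside the protocol and for unblinding. Withdrawal and loss to follow-up come on top, and the analysis uses a per-protocol set as well as ITT.

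**Working it through.** **Inputs** (Sample size, unless noted): p1 = 0.632 (placebo), p2 = 0.385 (QTF), difference 0.247; one-sided alpha 0.025, z = 1.960; power 80%, z = 0.8416; allocation 1:1 (Randomization and blinding); dropout 20%; enrolment 72 per arm. One-sided 0.025 and the two-sided 0.05 of Statistical analysis use the same critical value, so the difference in wording does not change n.

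**Step 1. Reproduce 61.** Unpooled normal approximation:

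n = (z_alpha + z_power)² × [p1(1 − p1) + p2(1 − p2)] / (p1 − p2)²

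= (1.960 + 0.8416)² × (0.632 × 0.368 + 0.385 × 0.615) / 0.247²

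= 7.849 × 0.46935 / 0.061009 = 60.4, so **61 per arm**.

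This matches the protocol exactly, with no allowance for dropout. Other formulas for the same inputs do not give 61: pooled variance 63.1 (64), arcsine 63.0 (63), continuity-corrected 71.

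**Step 2. Apply the stated dropout.**

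| Route | Per arm | Total |
|---|---|---|
| 61 / (1 − 0.20) = 76.25 | 77 | 154 |
| 61 × 1.20 = 73.2 (shortcut, under-provides) | 74 | 148 |
| 61 / (1 − 0.15) = 71.8 | 72 | 144 |
| Protocol | 72 | 144 |

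The stated total is 154 − 144 = 10 patients short (10/154 = 6.5%). Starting from the pooled figure of 64, 20% loss would need 64/0.80 = 80 per arm, 160 in total.

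**Step 3. What 72 per arm supports.** The largest loss that still leaves 61 is 1 − 61/72 = 15.3%. At 20% loss, 72 × 0.80 = 57.6 per arm remain.

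**Step 4. Power at that number.** Unpooled: power = Φ(0.247 / √(0.46935/n) − 1.960). At n = 57 this is Φ(2.722 − 1.960) = Φ(0.762) = 77.7%.

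| Evaluable per arm | Unpooled formula | Pooled formula | Chi-square test, exact power | Fisher's exact test |
|---|---|---|---|---|
| 57 | 77.7% | 75.8% | 75.7% | 69.3% |
| 58 | 78.4% | 76.5% | 76.9% | 70.8% |
| 61 | 80.4% | 78.6% | 80.4% | 74.9% |
| 72 (no outcome lost) | 86.4% | 85.0% | not computed | 81.9% |

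Statistical analysis names chi-square or Fisher's exact test for the recurrence rate, so those columns are shown beside the formula behind the 61.

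**The case against.** The mismatch itself is hard to dispute. The case on the other side concerns its origin and weight.

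- **72 may not come from 15%.** The unrounded 60.38 × 1.2 = 72.46, which rounds to 72, and 60 × 1.2 = 72 exactly. The authors may have added 20% before rounding up. This stands: 15% is the allowance to which 72 is equivalent, not proof of what was assumed. But that route still leaves 57.6 per arm after 20% loss, so the error remains.
- **The pooled and Fisher figures bring in a second issue.** This is partly right. Pooled power is already 78.6% at the full 61, so dropout explains only part of that gap. Expected cell counts near 28 or 29 give no small-sample reason to use Fisher's test. The loss due to dropout alone is best read from the unpooled column, about 2 points below target.
- **These powers are for a comparison of flare rates.** The primary outcome, the number of flares, is assigned to a t-test or Wilcoxon test. That is true, but the protocol chose to size the trial on rates, and the inconsistency lies within that calculation.
- **ITT may recover the loss.** If all 72 per arm supplied outcomes, power would be about 85% to 86% by the two normal-approximation formulas. That is correct, but a dropout inflation assumes that dropouts are not evaluable, and the protocol says it made one.
- **The study calls itself exploratory and concedes a small sample.** That may make 76% to 78% power acceptable. It does not make the printed figure correct.

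**Conclusion.** The concern holds. The 61 per arm is correct before dropout; the step from 61 to 72 is wrong for the stated 20%. The stated inputs require 77 per arm (154 in total), so the plan is 10 patients short. With 72 per arm and 20% loss, power is 77.7% to 78.4% by the formula that gives 61, and 75.8% to 76.5% by the pooled formula.

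This assumes the stated flare rates, equal loss in both arms and no outcome from patients who drop out. The shortfall is about 2 to 4 points. It does not bias the treatment estimate or raise the type I error, but it makes a headline design figure untrue as written.

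**What to change.** Keep 144 and correct the Sample size sentence in one of two ways:

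1. If the team actually assumed 15% loss, say so: 61/0.85 = 71.8, hence 72 per arm.
2. If 20% is the real expectation, keep it and state that 57 to 58 evaluable per arm give about 76% to 78% power.

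The second option follows directly from what the document states. The first should be used only if 15% was the planning assumption, not because it fits the total. In either case name the formula (unpooled Z or chi-square), since 61 comes from the unpooled version and the pooled version needs 64.

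The cost is one corrected sentence and a slightly less favourable claim, with no added patients. If both 20% loss and 80% power are to stand, enrolment would have to rise to 77 per arm (154 in total).

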### Ethics, oversight, and dissemination

This trial has received approval from the Ethics Committee of Zhejiang Chinese Medical University, with approval number 20240329−6. All participating centers have obtained approval from their respective local institutional review boards. The Ethics Committee of Zhejiang Chinese Medical University will oversee the entire process of the trial, including assessing the status and quality of the research, such as recruitment rates, dropout rates, and AEs. Researchers will promptly address any AEs reported by patients or their families. The results of the RCT will be published in peer-reviewed journals, ensuring patient anonymity by not disclosing their names unless required by law. Access to patient information will be restricted to authorized individuals who will strictly manage data according to government and legal regulations.

### Randomization and blinding

A multi-center competitive stratified block randomization method was utilized. Random numbers for the multi-center group were generated using the corresponding randomization procedure in SAS software (version 9.4). These random numbers, alongside their corresponding drug codes, functioned as unique identifiers for participants. After conducting necessary baseline assessments, all eligible patients who met the inclusion criteria and signed informed consent forms will be randomly assigned to either the intervention or control group in a 1:1 ratio. The randomization design and numbers were provided by Jiangsu Famous Medicine Co., Ltd. The relevant parameters and results of the randomization scheme will be recorded by Zhejiang Chinese Medical University (the research design unit). Apart from the outcome evaluators and staff at the drug production center, all researchers and patients remained unaware of treatment allocation. The QTF granules and placebo granules were identical in odor, color, and packaging, ensuring blinding. Distribution details will be disclosed to researchers only when necessary for drug administration. Products were delivered directly to patients according to their allocation codes. In emergencies, the research design unit will promptly provide researchers with randomized numbers and treatment allocations. All participants will strictly adhere to confidentiality regulations to protect patients’ personal privacy information.

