**Method:**

This is a multi-center, randomized, double-blind, placebo, parallel-controlled clinical trial conducted in four hospitals in Zhejiang Province, China. A total of 144 patients, aged 18–80 years, will be randomly allocated to either the intervention group (QTF + febuxostat) or the control group (placebo + febuxostat) for a 12-week treatment period. The primary outcome measure is the frequency of gout flares. Secondary outcome measures include the time from the patient’s enrollment to the first occurrence of gout flare (in days), duration of gout flare (in days), health assessment questionnaire disability index (HAQ-DI), pain level (visual analog scale – VAS), rate of achieving target uric acid levels. Occurrences of adverse events, and results from electrocardiograms and laboratory tests, will be monitored.

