## Methods

### Study design

A multi-center, randomized, double-blind, placebo, parallel-controlled clinical trial will be conducted in four hospitals across the province of Zhejiang, including the First Affiliated Hospital of Zhejiang Chinese Medical University, the Second Affiliated Hospital of Zhejiang Chinese Medical University, Shengzhou People’s Hospital, and Huzhou Hospital of TCM.

This protocol adheres to the SPIRIT 2013 reporting checklist prohibit [23]. The study will also proceed according to the Declaration of Helsinki (as revised in 2013). The entire study flowchart and follow-up procedures are illustrated in Fig 1 and Fig 2, respectively.

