### Intervention

The visit schedule is set for weeks 0, 6, 12, 24, and 48. Visits at weeks 0, 6,12, and 24 will be conducted offline, with patients attending the hospital to have relevant information collected by the responsible physician. The visit at week 48 will be conducted online (via phone calls or WeChat).

Conventional treatment: Both groups receive ULT, which in this study is stipulated as febuxostat 40 mg once daily.

TCM Treatment: The intervention group receives QTF granules, while the control group is administered placebo granules, with treatment lasting for 12 weeks. QTF granules constitute a Chinese herbal compound, and the composition of the granules is detailed in Table 2. The placebo granules utilized in this study contain 10% of the same components found in QTF granules. All QTF granules and placebo granules are manufactured and packaged by Jiangyin Tianjiang Pharmaceutical Co., Ltd., located in Jiangsu Province, China. There are no discernible differences in appearance, color, odor, or weight between the QTF granules and placebo granules. The quality of these granules underwent inspection by authorized agencies before declaration, ensuring compliance with specified quality standards. Each dose of QTF granules or placebo granules consists of 9.8g per sachet, to be taken twice daily with 200 ml of warm water, continuously for 5 days followed by a 2-day rest period.

**Table 2 pone.0327864.t002:** Components of Qu-zhuo Tong-bi formula granules.

Chinese name	Latin name	Parts of the substances	Amount (g)
Tu Fu Ling	*Smilacis Glabrae Rhizoma*	Root and rhizome	60
Bi Xie	*Dioscoreae Hypoglaucae Rhizoma*	Root and rhizome	30
Yu Mi Xu	*Stigma Maydis*	Style and stigma	15
Chao Yi Yi Ren	*Coicis Semen*	Mature seed	30
Xi Xian Cao	*Siegesbeckiae Herba*	Aboveground parts	18
Jiang Huang	*Wenyujin Rhizoma Concisum*	Root and rhizome	12
Sang Ji Sheng	*Taxilli Herba*	stem or branches with leaves	15
Yan Hu Suo	*Corydalis Rhizoma*	Root tuber	18
Fo Shou	*Citri sarcodactylis Fructus*	Mature fruit	12

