### Outcomes

#### Primary outcomes.

The frequency of gout flares will be recorded at weeks 6, 12, 24, and 48.

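### As written, the blinding paragraph says that outcome evaluators know the treatment allocation, which conflicts with the double-blind label and must be corrected or justified

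*Protocol article*

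**What the plan says.** The Abstract (Method) describes the design with the words "This is a multi-center, randomized, double-blind, placebo, parallel-controlled clinical trial". The title, the Introduction and the Study design section use the same label; Study design has "A multi-center, randomized, double-blind, placebo, parallel-controlled clinical trial will be conducted in four hospitals across the province of Zhejiang".

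The section on randomization and blinding then says who is blinded: "Apart from the outcome evaluators and staff at the drug production center, all researchers and patients remained unaware of treatment allocation". It gives product matching as the means of blinding: "The QTF granules and placebo granules were identical in odor, color, and packaging, ensuring blinding". It adds a conditional disclosure: "Distribution details will be disclosed to researchers only when necessary for drug administration". The same paragraph has products delivered straight to patients by code, and has the research design unit release allocations in an emergency.

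The primary outcome is flare frequency: "The frequency of gout flares will be recorded at weeks 6, 12, 24, and 48". The secondary outcomes include time to first flare, flare duration, HAQ-DI, VAS pain and the rate of reaching the uric acid target. For the hospital visits the Intervention section describes data collection as "with patients attending the hospital to have relevant information collected by the responsible physician". For a flare during treatment it has the patient contact research personnel for a VAS assessment.

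**The concern.** Outcome evaluators are the staff for whom knowledge of the arm does most harm, because they can influence what is recorded as an event. The sentence on blinding names them as an exception to it. This is a positive statement about who knows the allocation. It is not a detail that a condensed article has left to the full protocol.

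Flare frequency is not a laboratory measure. Someone has to ask about a flare, accept it as one, separate it from the previous one, and date its start and end. An evaluator who knows the arm could do any of these differently between arms, in either direction and without intending to. Time to first flare and flare duration rest on the same steps. If the sentence describes practice, the trial could not claim blinded outcome assessment for its main result, whatever its title says.

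**Working it through.** No arithmetic applies. The point concerns who is blinded, and it changes no figure in the article. The check sets the relevant statements side by side.

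1. **Plain meaning of the sentence.** It names two exceptions, the outcome evaluators and the drug production staff, and says that everyone else was unaware. The exceptions are therefore the groups not kept unaware. For production staff this is expected. For evaluators it is not.

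2. **Contradicting text.** The title, Abstract, Introduction and Study design section all say double-blind. None of them, and no other section, says that the evaluators are blinded. The label conflicts with the sentence but does not override it.

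3. **Does product matching cure it?** Identical granules protect people who see only the product, that is, patients and treating staff. They do not protect a person who has been given the allocation.

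4. **Which outcomes are exposed?** The article does not say which outcomes the evaluators assess.
   - *Flare count, time to first flare, flare duration:* exposed as far as evaluators elicit, confirm, count or date flares.
   - *VAS and HAQ-DI:* partly protected, because the patient gives the rating and is stated to be blinded. How the answer is obtained and recorded could still matter.
   - *Rate of reaching the uric acid target:* a laboratory value, with little room for assessor judgement.
   - *Causality of adverse events:* a judgement in five levels, but the Safety outcomes section does not say who makes it.

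5. **Are the evaluators the same people as the treating staff?** The article does not say whether they are the responsible physicians of the visit schedule or the research personnel contacted at a flare. If they are separate, treating staff stay blind and the assessors do not. If they are the same, the treating physicians know the arm as well, and double-blind fails even in its narrow sense of patients and treating staff.

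6. **The disclosure sentence.** Sachets are matched, coded and delivered directly, and emergencies have their own route, so routine administration has no evident need for the arm. If distribution details means kit or code numbers, the sentence is harmless. If it means the arm, it is a second exception to blinding. The emergency sentence speaks of treatment allocations, a different term, so the text leaves both readings open.

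**The case against.** The strongest reply is that this is a slip of language. The article has others: a stray word after the reference to the SPIRIT checklist, and a Statistical analysis section that calls time to first flare count data and the recurrence rate measurement data. The blinding paragraph also has the research design unit release allocations in an emergency. That unit must therefore have access to the code, yet it is not among the named exceptions, which suggests loose drafting. The exit criteria list unblinding during the trial as a ground for leaving it, which fits poorly with evaluators unblinded by design. This objection stands in part: a slip is a real possibility. But nothing in the article states the opposite, and a wrong statement on blinding in a published protocol needs correction too.

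A second reply is that double-blind commonly refers to patients and treating staff. Even so, assessment of the primary outcome would remain unblinded.

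A third is that patients are blinded and much of the data is patient-reported. This stands for the patient's own VAS and HAQ-DI ratings. It does not fully protect the confirming, counting and dating of flares.

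A fourth is that no section gives the evaluators any particular task. This stands, and it limits the conclusion to whatever part they play.

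**Conclusion.** The point holds as a defect of the text: the article's only statement on evaluator blinding says that evaluators are not blinded, against a double-blind label used throughout. It must be corrected or justified. The consequence for the primary outcome is conditional on two things that the article does not settle: that the sentence is followed in practice, and that evaluators have a part in establishing flares.

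The size of any bias cannot be estimated. The article gives no share of flares that depend on judgement and no error rate for assessors, so a figure in percentage points would be invention.

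A reader might infer three stronger things that the document does not support:

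- **That assessment is in fact unblinded.** The text shows a conflict between two statements. It does not show what evaluators have been given.
- **That treatment arms are routinely disclosed to researchers.** The sentence on distribution details is ambiguous and may refer only to kit or code numbers.
- **That the company's several roles break the blind.** One company supplies the randomization numbers, the data system and the analysis. That is not an error in itself, nothing says that its analysts or data managers see the list, and its internal separation is properly left to the full protocol or SAP.

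**What to change.** First establish which case applies: whether any outcome evaluator has, or is meant to have, access to the allocation.

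**If not**, replace the sentence with a statement that patients, investigators and outcome evaluators stay blinded until database lock, and that only the holder of the randomization list and the packaging staff know the allocation. Either say that distribution details are kit or code numbers and never the arm, or delete that sentence, so that emergency unblinding is the only route to the allocation. The cost is a two-sentence amendment, a correction to the article and an instruction to the four sites. The granules are already matched and coded, so no extra staff are needed.

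**If evaluators already hold the allocation**, make the same changes, but rewording cannot undo what is known. Disclose it, and have flare outcomes assessed from then on by existing study staff who are still blinded. Do not claim blinded outcome assessment for the data already collected. The cost is then a reassignment of duties and a lasting limitation to report with the results.
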